### Therapist selection, training, supervising, and monitoring

Prior research suggests it is important to have 2 clinicians (at least master’s level educated) running the intervention together as co-facilitators, matching race of the participants to race of the group facilitators. There will be two different teams of therapists for each condition; the principal investigator (PI) will hire 1 licensed clinical supervisor and at least 3 master’s level educated AA therapists who will be trained to provide either FFCT or PED. The clinical supervisor will have at least a doctoral degree and 5 years of experience doing family-based therapy. The therapists will have at least 2 years of family therapy training or experience and at least a master clinical degree. The PI and project manager will train the clinical supervisor and therapists. Training will begin with reading the treatment manual and attending a training workshop. The workshop will focus on program content, including sensitivity to cultural and socioeconomic status differences. The PI will certify the therapists using the adherence measures; they must receive an average rating of 5 or higher (7-point scale). Once the trial begins, the clinical supervisor will meet with the therapists weekly to review their video recorded sessions and complete the fidelity checklist for FFCT and PED sessions. In years 4 and 5 of the study, objective raters will be trained to rate adherence. Twenty percent of the video-recordings consisting of early middle and late sessions in the treatment will be rated.

### Blind assessors

Several steps will be taken to ensure the assessment team and adherence raters are blind to treatment assignment, in accordance with Consort 2010 guidelines including: (1) The assessment team will not work with clinical staff and will not attend meetings in which participants’ treatment assignment or progress is discussed. (2) Interviewers will be trained to not discuss participants’ involvement in the project with the subject. (3) At the start of each interview, participants will be given a card asking them not to mention which treatment they received. These procedures should limit staff’s influence on participant report; any breaking of “blindness” will be documented and reported according to Consort guidelines.

### The treatment models: (FFCT) and (PED)

Families Fighting Cancer Together (FFCT) is a culturally sensitive manualized, empirically supported, brief (5 sessions; 1 session every other week over 8 weeks) family support group program designed to help African American (AA) families cope with the stress of solid tumor parental cancer. FFCT derives from an integration of the research team’s previous studies with racially diverse samples of parents coping with cancer and their adolescents [28, 8, 9, 22, 27].

FFCT is characterized by four key features that address the particular needs of low-to-middle income AA families: (1) Therapists focus heavily on engagement and reduction of logistical (e.g., financial and transportation barriers) as well as psychological barriers (e.g., stigma, treatment readiness, negative experience with the mental health system). (2) Caregiver is defined broadly to reflect the wide range of family structures common in AA families. (3) Intervention targets Afro-centric coping skills: (a) faith; (b) encouraging fictive kin instrumental and emotional support; (c) highlighting positives; and (d) encouraging flexibility in family roles. (4) The support group structure and emphasis on brief treatment with a specific problem focus is culturally congruent with AAs who tend not to prefer individual therapy because of the stigma associated with mental health treatment and who prefer an action-oriented therapeutic approach with short-term goals [18, 21, 29].

FFCT includes the following 5 sessions: Sessions 1 and 2 are 90-min adolescent support group sessions (up to 8 AA youth). Session 1 focuses on improving awareness and understanding about how their parents’ cancer is affecting them. The group facilitators focus on the promotion of empathy and understanding among group members, reducing tension, increasing fun activities, and maintaining normal routines. In session 2, the facilitators help adolescents develop adaptive coping skills and prepare youth to more openly communicate their thoughts, fears, and feelings to their parents about the cancer experience during sessions 4 and 5. Session 3 is a 2-h, parent-only support group session to help parents get ready to talk more openly to their adolescents during sessions 4 and 5. This session focuses on: (1) therapist alliance and trust building with parent(s); (2) improving parents’ self-care while navigating cancer; (3) teaching parents to listen and to validate their adolescent’s experiences so youth can more openly communicate fears and worries; and 4) promoting more open communication between parents and children using Afro-centric resilience. Sessions 4 and 5 includes two (2 h) interactive multiple family group sessions (up to 8 families). In session 4, group facilitators focus discussions on parental cancer and on the stress it places on families, in particular helping adolescents openly share their thoughts, feelings, and fears with parents and helping their parents to listen and validate them. Session 5 focuses on facilitating secure parent-child attachment, so adolescents can talk directly to their parents and parents can respond to their children’s worries/fears in a responsive and empathic way. Facilitators focus discussions during sessions 1 to 5 on faith, spirituality, resilience, and utilizing fictive kin and the African American community (e.g., the church) for practical, emotional, and spiritual support [30].

Psychoeducation (PED) consists of only parents receiving a 5-session (1 session every 2 weeks over 8 weeks) psycho-education group, which was adapted from an American Cancer Society (ACS) free online educational program [31]. This program, (previously known as *I Can Cope*) was developed for cancer patients, families, and friends. This standardized online program included self-paced lectures about cancer: managing treatments and side effects; eating healthily during and after treatment; and finding resources. Explicit permission was attained from ACS to use this program. The purpose for choosing this program as the PED comparison group was it closely resembled what oncology clinics offer to adult cancer patients [32]. The ACS’s structured PowerPoint lectures and videos from *I Can Cope* have recently been updated and organized differently. Group facilitators will cover the following in 5 (1-h) psycho-education sessions with the most current ACS informational materials: (1) managing effects of illness/treatment; (2) nutrition during treatment; (3) mobilizing resources/support; (4) addressing self-esteem/intimacy; and (5) integrating mind, body, and spirit. This comparison group controls for contact time with group facilitators, filling out baseline information, posttest, 6- and 12-month follow-up assessments; it also restricts the focus on parent-child communication and attachment in the experimental group (FFCT).

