#### Treatment Fidelity

Standardized fidelity treatment checklists were developed for FFCT and PED to monitor treatment integrity and dosage. These treatment checklists were tested in our previous pilot studies [22, 27]. Monitoring involves both dosage and purity; dosage of the intervention is measured by the completion of the number of sessions. Purity involves monitoring the extent to which the program was delivered as designed. All sessions will be video-recorded. Once the trial begins, the clinical supervisor will meet separately with the two teams of therapists weekly to review their video-recorded sessions, complete the fidelity checklist for both FFCT and PED sessions, and re-train as necessary to monitor treatment fidelity. Second, a random sample of 25% of all group sessions will later be rated by 2 coders blind to treatment assignment on the same checklist in years 4 and 5. With a total of 172 families (86 families/arm) who attend 5 (90-min to 2-h) support group sessions, it is estimated there will be 14 FFCT groups with 5 to 8 families/group and 14 PED groups with 5 to 8 families/group run during the course of this study. All intervention sessions will be video recorded using a HIPAA-compliant video system at and stored in an encrypted secure server; 50% of cases (*n* = 7 groups of PED and 7 groups of FFCT) will be reviewed after each session using a fidelity checklist. To minimize drift, the PI and project manager will review a random sample of 25% of FFCT cases (*n* = 4 groups) and 25% of PED cases (n = 4 groups) for each therapy team (2 therapists/team) to provide ongoing feedback. The clinical supervisor, PI, and project manager will view the video-recorded sessions and use the fidelity treatment checklists to monitor treatment integrity and dosage. After the PI and project manager review sessions each week, they will share feedback immediately with the clinical supervisor and 3 therapists and at monthly meetings with the intervention team to direct restraining efforts as needed.

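### PED is said to control for contact time, but adolescents, who report the primary outcome, get 7 hours of facilitator contact in FFCT and none in PED

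*Protocol article*

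**What the plan says.** The section on the treatment models describes FFCT session by session. For adolescents: "Sessions 1 and 2 are 90-min adolescent support group sessions". For parents: "Session 3 is a 2-h, parent-only support group session". For both together: "Sessions 4 and 5 includes two (2 h) interactive multiple family group sessions".

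The same section describes PED as a programme for parents only, with the same number of sessions at the same two-week spacing: "Group facilitators will cover the following in 5 (1-h) psycho-education sessions". It then states, without limiting the claim to parents or to the number of sessions: "This comparison group controls for contact time with group facilitators".

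The Treatment Fidelity section gives another session length. Speaking of all 172 families, 86 per arm, it describes families "who attend 5 (90-min to 2-h) support group sessions".

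The primary outcome is adolescent depressive symptoms at the end of treatment. Table 1 lists the adolescent as the source of the CDI-2.

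**The concern.** A comparator that controls for contact time is meant to rule out one explanation of a treatment difference: that participants improved because someone spent time with them. That protection has to apply to the people whose outcome is measured. Here they are the adolescents, and the PED arm offers them no group sessions.

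A significant negative FFCT coefficient in the primary ANCOVA could come from the programme's content, from time with facilitators, from time with other adolescents in the same position, or from a mixture. A reader who takes the contact-time statement at face value would think the attention explanations had been excluded. No analysis can recover the distinction, because planned adolescent contact is zero throughout one arm and so coincides with the treatment indicator.

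**Working it through.** The plan gives no total in hours, so there is no figure to reproduce. The claim implies equal facilitator contact in the two arms. The equality that can be confirmed is five sessions against five, one every two weeks over eight weeks.

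**Inputs** (section on the treatment models, unless noted)
- FFCT sessions 1 and 2: adolescents, 1.5 h each
- FFCT session 3: parents, 2 h
- FFCT sessions 4 and 5: parents and adolescents, 2 h each
- PED sessions 1 to 5: parents, 1 h each
- Alternative PED length, from Treatment Fidelity: 1.5 to 2 h each

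**Formula:** planned contact for a person = sum of the lengths of the sessions that person is due to attend.

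| Person | FFCT | PED, 1-h sessions | PED, 1.5 to 2-h sessions |
|---|---|---|---|
| Adolescent | 1.5 + 1.5 + 2 + 2 = 7 h | 0 h | 0 h |
| Parent | 2 + 2 + 2 = 6 h | 5 × 1 = 5 h | 5 × 1.5 = 7.5 h to 5 × 2 = 10 h |

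**Sensitivity to reading**
- If sessions 4 and 5 were taken to last 2 h in total (a strained reading), adolescents would have 1.5 + 1.5 + 2 = 5 h against 0 h, and FFCT parents 2 + 2 = 4 h. Contact is still unequal.
- The adolescent contrast does not depend on which PED length applies. The parent contrast does: FFCT parents have 1 h more than PED parents under one length and 1.5 to 4 h less under the other.
- The match in session number is a match of programmes, not of persons. An FFCT parent is due at three sessions (3, 4 and 5) and an FFCT adolescent at four (1, 2, 4 and 5). A PED parent is due at five and a PED adolescent at none.

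**The case against.** Four points can be made for the plan.

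- **The comparator is open and reasoned.** The abstract, the study design and the treatment section all say that PED is for parents only. The article explains that PED was chosen because it is close to the support that cancer clinics give adult patients. This stands: comparing a family programme with parent-only education is a legitimate question, and the choice of comparator is not the error.
- **The primary aim is already a package comparison.** Aim 1 compares FFCT with PED. A reader might infer that the trial claims to isolate the culturally adapted content. No aim or analysis says so, and that stronger charge should not be made. The treatment section does present PED as a control for contact time and as leaving the communication and attachment work to FFCT, so the sentence still invites an interpretation that the design cannot support.
- **Parents are nearly matched.** At one hour per PED session they get 6 h against 5 h. This stands, conditionally on that length. The sentence is not limited to parents, however, and parents do not report the primary outcome.
- **The conflict over session length may be loose wording.** The article uses the term support group for FFCT, so the Treatment Fidelity phrase may have been meant for that arm alone. Grammatically it covers all 172 families, and the text does not settle the matter.

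A tempting headline is 9 hours against 5 per family (3 + 2 + 4 = 9; 5 × 1 = 5). It adds sessions attended by different people, so no FFCT participant receives 9 h. It also depends on the disputed PED length: with 7.5 to 10 h the family totals could roughly agree. It should not carry the point.

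**Conclusion.** The contact-time statement is wrong for the people who supply the primary outcome. Planned adolescent contact with facilitators is 7 h in FFCT and none in PED (5 h against none on the strained reading), and no reading of the session lengths changes the zero. For parents the planned difference is 6 h against 5 h if PED sessions last one hour, and unresolved otherwise. These are planned hours at full attendance.

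The consequence is one of interpretation. A reader might go further and infer that the randomised comparison is biased or that the trial needs another comparator. The documents do not support that: the randomised contrast still estimates the effect of one package against the other, and neither the sample size nor the primary test rests on equal contact. What the trial cannot do is attribute a CDI difference to FFCT content rather than to attention given to the adolescent. The correction should be made because it changes what the main result may be said to show.

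**What to change.** 1. Replace the contact-time statement with wording such as: *matched for number and spacing of sessions and for assessments, not for contact time; adolescents in PED have no facilitator contact*.
2. State the primary conclusion as the effect of the FFCT package (content plus adolescent contact) against parent-only education.
3. Reconcile the PED session length in the treatment section with the length in Treatment Fidelity. The documents do not show which is right.
4. Report sessions attended by arm, separately for parents and adolescents. The plan counts dosage in sessions completed, so minutes may not be on the fidelity checklists. All sessions are video-recorded, so durations can be taken from the recordings if wanted.

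The cost is a few changes of wording, a small descriptive table (with some extra extraction if durations are included) and a narrower efficacy claim. The point calls for no change to the comparator, sample size or primary analysis.

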#### Treatment Fidelity

Standardized fidelity treatment checklists were developed for FFCT and PED to monitor treatment integrity and dosage. These treatment checklists were tested in our previous pilot studies [22, 27]. Monitoring involves both dosage and purity; dosage of the intervention is measured by the completion of the number of sessions. Purity involves monitoring the extent to which the program was delivered as designed. All sessions will be video-recorded. Once the trial begins, the clinical supervisor will meet separately with the two teams of therapists weekly to review their video-recorded sessions, complete the fidelity checklist for both FFCT and PED sessions, and re-train as necessary to monitor treatment fidelity. Second, a random sample of 25% of all group sessions will later be rated by 2 coders blind to treatment assignment on the same checklist in years 4 and 5. With a total of 172 families (86 families/arm) who attend 5 (90-min to 2-h) support group sessions, it is estimated there will be 14 FFCT groups with 5 to 8 families/group and 14 PED groups with 5 to 8 families/group run during the course of this study. All intervention sessions will be video recorded using a HIPAA-compliant video system at and stored in an encrypted secure server; 50% of cases (*n* = 7 groups of PED and 7 groups of FFCT) will be reviewed after each session using a fidelity checklist. To minimize drift, the PI and project manager will review a random sample of 25% of FFCT cases (*n* = 4 groups) and 25% of PED cases (n = 4 groups) for each therapy team (2 therapists/team) to provide ongoing feedback. The clinical supervisor, PI, and project manager will view the video-recorded sessions and use the fidelity treatment checklists to monitor treatment integrity and dosage. After the PI and project manager review sessions each week, they will share feedback immediately with the clinical supervisor and 3 therapists and at monthly meetings with the intervention team to direct restraining efforts as needed.

#### FFCT/PED adherence assessment and analysis

In years 4 and 5, two external adherence raters will be trained to code adherence on a random sample of 25% of video- recorded cases for the FFCT and PED treatment, even though PI and supervisor ratings will occur throughout the trial. The two adherence training manuals and the rating scales from both treatments will be integrated into one manual and one adherence measure. Two raters who will be blind to the aims of the study will also be trained. Twenty-five percent of cases (4 FFCT groups, 5 sessions/group × 4 groups = 20 sessions and 4 PED groups, 5 sessions/group × 4 groups = 20 sessions) will be randomly selected from each treatment condition. Adherence raters will be 2 undergraduate psychology students recruited from area universities. In order to train the raters (20 h of required training), the integrated manuals and scales will be given to them to read thoroughly. They will also read excerpts from pilot cases that reflect low, medium, and high extensiveness for each of the adherence items. In addition, the raters will review practice videos, also from the pilot. The raters will meet with the team weekly to discuss, as a group, their scores and questions about items, as well as resolve scoring discrepancies. We will derive inter-rater reliability through interclass correlation coefficients (ICC) per Shrout and Fleiss [33] through variance components models, assessing variability between the two raters compared to the total variability in adherence scores. Once the raters have obtained adequate inter-rater reliability with evaluation team and among themselves (ICC > .70) for each item, they will rate actual sessions from the study. Analysis will then focus on whether the therapists delivered the two treatments as intended.

#### Study measures/assessments

This study uses valid and reliable measures, all of which were used in our most recent pilot study with AA families, where there was no evidence or report of respondent burden or fatigue. The assessment schedule appears in Table 1.

**Table 1 Tab1:** Assessment Schedule

	*Source*	*Wk 0*	*Wk 8*	*Wk 24*	*Wk 52*
*General and Program Descriptive*					
*Demographic Family Survey*	*Parent*	*∙*			
*Consumer Satisfaction*	*Adol/Parent*		*∙*		
*Adolescent Psychological Outcomes*					
*Child Depression Inventory (CDI-2)*	*Adol*	*∙*	*∙*	*∙*	*∙*
*Revised Child Manifest Anxiety Scale (RCMAS-2)*	*Adol*	*∙*	*∙*	*∙*	*∙*
*Parent Psychological Outcomes*	*Parent*	*∙*	*∙*	*∙*	*∙*
*State-Trait Anxiety Inventory (STAI)*	*Parent*	*∙*	*∙*	*∙*	*∙*
*Center Epidemiological Depression Scale (CES-D)*	*Parent*	*∙*	*∙*	*∙*	*∙*
*The Functional Assessment of Cancer Therapy FACT-G (version 4)*	*Parent*	*∙*	*∙*	*∙*	*∙*
*Parent-Adolescent Relational Outcomes*					
*Security Scale*	*Adol*	*∙*	*∙*	*∙*	*∙*
*Short Form Interaction Behavior Questionnaire (IBQ)*	*Adol/Parent*	*∙*	*∙*	*∙*	*∙*
*General Communication*	*Adol/Parent*	*∙*	*∙*	*∙*	*∙*
*Treatment Moderators*					
*Parenting Concerns Questionnaire (PCQ)*	*Parent*	*∙*	*∙*	*∙*	*∙*
*Helpful Group Experiences (HGE)*	*Parent*		*∙*		

##### Adolescent psychological outcomes

ᅟ

#### Depression

The most widely used self-report measure is the *Children’s Depression Inventory (CDI-2)*, which was adapted from the Beck Depression Inventory (BDI) and is reliable and valid for children 7 to 18 years of age [34]. The CDI-2 includes 28 items that assess behaviors associated with depression (e.g., sleep disturbance, anhedonia, suicidality, and appetite loss). Items are rated on a 3-point scale. Raw scores are converted to T scores. T-scores of 70 and higher on the total 28-item CDI-2 scale indicate severe symptoms of depression and is an exclusion criterion. For this study, a cutoff score of 70+ or higher on the T-score will be used to screen out AA adolescents because it indicates severe levels of depressive symptoms [35, 36].

#### Anxiety

The *Revised Children’s Manifest Anxiety Scale (RCMAS-2)* includes 49 items, rated as true or not [37]. The *RCMAS-2 yields scores for six scales*: 1) *Inconsistent Response* (INC; 9 pairs) index—new; 2) *Defensiveness* (DEF; 9 pairs)—renamed; was Lie. 4 Anxiety scales: 3) *Total Anxiety* (TOT; 40 items); 4) *Physiological Anxiety* (PHY; 12 items); 5) *Worry* (WOR; 16 items)—renamed—was Worry/oversensitivity; and 6) *Social Anxiety* (SOC; 12 items)—renamed—was Social Concerns/Concentration. Extensive reliability (α = .85 and adequate internal consistency), validity (e.g., correlation of .85 with State-Trait Anxiety Inventory [STAI] for Children and significant correlation with teacher observations), and normative data have been documented. A cutoff score of 71 (T-score) or higher will be used to screen out AA adolescents with severe anxiety [37].

##### Adult psychological outcomes

ᅟ

#### Anxiety

The *State-Trait Anxiety Inventory (STAI)* will be used to measure anxiety [38, 39]. It includes 40 items (4-point Likert scale), approximately half of which are worded positively (e.g., “I feel regretful” about anxiety that is present) and the other half, negatively (e.g., “I feel pleasant” about anxiety that is absent). The STAI is a reliable and valid measure of state and trait anxiety [38].

#### Depression

The *Center for Epidemiological Studies Depression Scale (CES-D)* is a widely used, 20-item self-report scale that measures the current level of depressive symptoms in the general population, with an emphasis on depressed mood during the past week [40]. Scores range from 0 to 60, with higher scores indicating more symptoms of depression. CES-D scores of 16 to 26 are considered indicative of mild depression, and scores of 27 or more indicate major depression among medical patients.

